### Measurement planning

Outcome measurement was planned according to time points specified in the timetable in figure 1. Briefly, the procedure was as follows: When patients were willing to participate, we arranged a visit with an independent research nurse. During this visit, patients signed a consent form, baseline data were recorded and instructions were given on the use of the diary and questionnaires.

**Figure 1 F1:**
[figure not shown]
**Timetable**. Schematic representation of successive time points for data collection, reported for all outcome measures and questionnaires. * 23 irradiations: outcome measurement was planned at approximately 23 irradiations, with a minimum of 20 and a maximum of 26 irradiations. ** End of therapy: measurement was planned at the end of the treatment. When more than 46 irradiations were needed, measurement was planned at 46 irradiations. *** Follow-up: Starting at the end of the therapy (or at the 46^th ^irradiation, see **), follow-up measurements were planned every 2 months, for up to 1 year after the last irradiation.

Immediately after this first visit, patients were randomised using the baseline data (information on the recruiting hospital and any previous experience of the patient with UV therapy were used to determine the randomisation strata). Both patient and attending dermatologist were informed about the type of treatment assigned, and the treatment was started accordingly. When (sometimes after a waiting period) the therapy was started, the patients did a SAPASI-assessment and began using the study diary. At approximately 23 (20–26) UVB treatments ànd at the end of the therapy (or 46 treatments) the patients received a series of questionnaires at home. Visits to the previously mentioned research nurse were scheduled for the same time points. Throughout the whole trial, the independent research nurse was not informed about the randomisation results and therefore remained blinded.

For all UVB therapies lasting longer than 46 treatments, a cutoff point of maximally 46 treatments was used to establish effectiveness. The choice of 46 as the maximum number of treatments was derived from unpublished data from the home care organisations about the treatment duration of their patients.

At the end of the therapy (or 46 treatments), 105 patients were followed for 12 more months to monitor long term effectiveness and cost. The patients received a short questionnaire at home every 2 months and returned this questionnaire by mail. At the end of the follow-up, information on medication use during the trial period was retrieved retrospectively for each patient from his/her pharmacist.

### Ethics & informed consent

The final protocol was approved by the Medical Ethics Committees of all participating hospitals. Patients were able to quit the study at any time. Informed consent was obtained after the study objectives, types of therapy, benefits and risks, and the concept of randomisation had been explained extensively. The study was performed according to the principles of Good Clinical Practice [34].

### Statistical analysis

All data will be analysed according to the intention to treat principle, meaning all included patients will be analysed according to the group they were randomised to. This includes patients who dropped out or changed therapy. The statistical methods that will be used are chosen in accordance with the type of data that is available. For continuous data differences and their 95% Confidence Intervals (95% CIs) will be presented. In case of binary outcomes, differences in proportion with 95% CIs will be calculated. Whether randomisation was successful will be determined by assessing comparability of baseline characteristics. No formal statistical tests are foreseen. In the event apparent differences are noted, a multivariate analysis will be performed to adjust for potential confounding.

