### Randomisation procedure

Every patient eligible for UVB phototherapy who was willing to participate in the study was registered at the central coordination centre. After providing informed consent and registration of baseline data a randomisation number corresponding with either home or outpatient phototherapy was drawn from a computer-generated list. Randomisation took place using stratified randomisation, in particular the minimisation method described by Pocock [19]. This method assigned the two treatments taking into account the recruiting hospital and possible previous experiences with UV phototherapy. After randomisation, both patient and dermatologist were informed of the assigned treatment, and this treatment was started according to standard procedures.

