#### Effectiveness

Assessment of effectiveness of both UVB treatments will take place through calculation of the PASI and SAPASI-scores for both treatment modalities at regular points in time, and subsequently calculating differences in (SA)PASI scores over time. Possible differences in effectiveness between the two therapies will be established through comparison of differences in (SA)PASI scores inclusive of 95% CIs. The side effects of the therapy were reported for each irradiation as being present ("yes") or not being present ("no"). For each type of side effect the answers will be compared on a group level and presented with their 95% CIs.

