#### Quality of life (QoL)

Continuous sum-scores of the QoL questionnaires will be compared by calculating differences in QoL and their 95% CIs. Changes in QoL will also be compared across groups.

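### Covariate adjustment depends on baseline differences that look apparent, so the minimisation factors would practically never enter the comparison and the baseline score is not a covariate

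*Protocol article*

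**What the plan says.** The Statistical analysis section of the protocol article plans differences with 95% confidence intervals for continuous outcomes. For the others: "In case of binary outcomes, differences in proportion with 95% CIs will be calculated". On baseline balance it says "Whether randomisation was successful will be determined by assessing comparability of baseline characteristics", then "No formal statistical tests are foreseen", and then gives its only rule on covariates: "In the event apparent differences are noted, a multivariate analysis will be performed to adjust for potential confounding".

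Under Statistical analysis, Effectiveness, PASI and SAPASI are handled by "subsequently calculating differences in (SA)PASI scores over time", and the treatment comparison reads "Possible differences in effectiveness between the two therapies will be established through comparison of differences in (SA)PASI scores inclusive of 95% CIs". No covariate is named there. For quality of life, sum-scores are compared directly, and "Changes in QoL will also be compared across groups".

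On allocation, the Randomisation procedure section says of minimisation: "This method assigned the two treatments taking into account the recruiting hospital and possible previous experiences with UV phototherapy". Table 3 shows the resulting split for 196 patients.

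**The concern.** The rule makes adjustment depend on what the baseline table happens to show. It does not say how large a difference must be, which variables are inspected, which enter the model, or whether the adjusted or the unadjusted result is the main one.

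It also selects the wrong covariates. A covariate improves the comparison when it predicts outcome, whether or not it is out of balance. Hospital and previous UV phototherapy were judged important enough to steer allocation. Because allocation balanced them, a rule that looks for imbalance will pass them over. An analysis that ignores factors balanced by design reports a standard error that is too large wherever those factors matter. Separately, comparing changes from baseline is less efficient than using the baseline score as a covariate.

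At stake are precision, in a trial that hopes to show similar effectiveness, and a main estimate that is settled before the data are inspected.

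**Working it through.** **1. The plan's own figure.** The Sample size section gives 90 per group for 85% response and a 15-point difference, at α = 0.05 and 80% power. Read as a non-inferiority calculation at one-sided 0.025 (the article does not state sidedness), n = 2p(1−p)(z₀.₉₇₅ + z₀.₈₀)²/d² = 2 × 0.85 × 0.15 × (1.9600 + 0.8416)² / 0.15² = 0.255 × 7.849 / 0.0225 = 88.95, so 89. That agrees with 90. Nothing below disputes it or changes the required number.

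**2. Can the trigger reach the minimisation factors?** Table 3 gives previous UV phototherapy 50 against 50 (yes) and 48 against 48 (no). Across 14 hospitals the largest gap is 2 patients (5 against 3). Both columns sum to 98. There is no difference here that anyone would call apparent.

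**3. How often would it fire on other variables by chance?** With 98 per group the standard error of a standardised mean difference is √(2/98) = 0.143. The chance of exceeding an assumed cut-off on one variable is:
- 0.1: 48%
- 0.2: 16% (0.2/0.143 = 1.40)
- 0.3: 4%

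For at least one of 10 independent variables at 0.2, it is 1 − (1 − 0.162)¹⁰ = 83%. Whether adjustment happens therefore turns on an unstated cut-off and on how many variables are inspected.

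**4. Baseline score as a covariate (PASI and SAPASI changes).** With equal variances at baseline and follow-up and correlation r, the variance is proportional to 2(1 − r) for the change score and 1 − r² for ANCOVA. The ratio is (1 + r)/2, and the interval width scales with its square root:
- r = 0.3: √0.65 = 0.806, 19% narrower
- r = 0.5: √0.75 = 0.866, 13% narrower
- r = 0.7: √0.85 = 0.922, 8% narrower

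**5. Omitting the minimisation factors.** If they explain a share R² of outcome variance and are balanced, the unadjusted interval is too wide by a factor 1/√(1 − R²):
- R² = 0.05: 1.026, about 3%
- R² = 0.20: 1.118, about 12%

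**6. Simulation check.** Assumptions: the Table 3 hospital sizes, 196 patients, minimisation with assignment probability 0.9, a previous-UV effect of 0.4 SD, r of 0.3 to 0.7, hospital intraclass correlation (ICC) of 0 to 0.15, 3000 runs per setting. Type I error at a nominal two-sided 5%:
- unadjusted change score: 4.1–4.8% with no hospital effect, 2.1–3.7% at ICC 0.15
- baseline score added only if its standardised difference exceeds 0.2: 1.8–3.6% over all settings
- baseline score, previous UV and hospital always included: 4.5–5.5% over all settings

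Power for an assumed 0.4 SD effect at ICC 0.05 (r = 0.3 / 0.5 / 0.7) was 67% / 81% / 96% unadjusted, 71% / 84% / 97% under the trigger, and 86% / 93% / 99% with adjustment fixed in advance. The cost of not adjusting is about 3 to 19 points of power.

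**7. Where step 4 does not apply.** It is for change scores. For a direct comparison of follow-up scores, which the quality-of-life section plans first, the ratio is 1 − r², giving about 5%, 13% and 29% narrower at r = 0.3, 0.5 and 0.7. Neither formula describes a difference in response proportions.

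**The case against.** The article never calls its comparisons unadjusted, and a condensed article may leave model covariates and the handling of 14 hospitals to a fuller plan that could name them. That has force: silence about covariates alone would not be a finding. But the article is not silent. It states when adjustment takes place, and that stated rule is what is poorly fixed.

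The multivariate analysis might also be meant only as an addition to the planned differences. The text allows that reading, but does not say so. Planning no significance tests of baseline balance is sound and should stay.

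Four stronger readings are tempting, and the document does not support them:
- **Baseline PASI is ignored.** It is not. It enters by subtraction in the change score and through the response definition in the Sample size section (at least 50% improvement from baseline). What is missing is its use as a covariate.
- **The trigger is judged on unblinded data.** The article does not say whether the analyst knows treatment labels or outcomes when baseline comparability is assessed.
- **The percentages show how far the 15-point margin is affected.** That margin concerns response proportions, whereas the ANCOVA figure concerns score changes. Nothing here quantifies whether adjustment would move an estimate across the margin.
- **The results will be biased or falsely positive.** The simulation shows error rates at or below nominal for the unadjusted and the triggered analyses. Wider intervals make similar effectiveness harder to claim, which is the cautious direction.

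**Conclusion.** The point holds and should be corrected. As stated, the rule leaves adjustment to an unspecified judgement about observed imbalance, and by construction it passes over the two factors used for allocation. The harm is lost precision and post hoc discretion.

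For PASI and SAPASI changes the loss is an interval that ANCOVA would narrow by about 19%, 13% or 8% at r = 0.3, 0.5 or 0.7. From the minimisation factors it is an interval about 3% to 12% too wide if they explain 5% to 20% of outcome variance. The correlation, the equal variances and the share of variance explained are all assumptions; the document gives none of them. Confidence is high that the trigger is badly fixed. The size of the loss is only indicative.

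**What to change.** Before outcomes are analysed, state the main model, to apply whatever the baseline table shows:
- **Scores:** ANCOVA of the follow-up value on baseline score, previous UV phototherapy and hospital. The baseline value should be one recorded before randomisation; according to Measurement planning, the SAPASI completed at the start of therapy comes after it.
- **Response:** a standardised (marginal) risk difference with its 95% confidence interval, from a logistic model adjusted for the same factors.
- **Hospital:** a random intercept, or pooling of the smallest centres.
- **Reporting:** keep the unadjusted difference as supportive, and label any adjustment prompted by observed imbalance a sensitivity analysis.

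The cost is analysis wording. Hospital and previous UV phototherapy were recorded for randomisation, and a baseline score is needed for the planned change scores anyway. The small downside is that 14 hospitals, two of them with only 3 and 4 patients, cannot all be fitted comfortably as separate fixed effects, hence the random effect or pooling.

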#### Effectiveness

Assessment of effectiveness of both UVB treatments will take place through calculation of the PASI and SAPASI-scores for both treatment modalities at regular points in time, and subsequently calculating differences in (SA)PASI scores over time. Possible differences in effectiveness between the two therapies will be established through comparison of differences in (SA)PASI scores inclusive of 95% CIs. The side effects of the therapy were reported for each irradiation as being present ("yes") or not being present ("no"). For each type of side effect the answers will be compared on a group level and presented with their 95% CIs.

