### Sample size

The sample size could not be calculated on the basis of presumed differences in effectiveness as there is no clear data available on the possible differences in treatment effects. However, based on the data available from a 1993 pilot study [16] and recent experience with home UVB phototherapy, we in fact expected the effectiveness of both therapies to be similar. The sample size was therefore calculated in accordance with a negative trial approach [17]. We considered a 50% or greater improvement in the psoriasis severity from baseline to be a relevant clinical response. A systematic review by Spuls et al. indicates that approximately 85% of the patients treated with UVB show at least a 50% improvement in their psoriasis [18]. Thus, with N = 90 per per treatment group and at α = 0.05 and β = 0.20 (power 80%), we would be able to show a difference in effectiveness of 15% or more; i.e., a reduction in effectiveness from 85% to 70% or less should be distinguishable. To allow for missing data and losses to follow-up (i.e. withdrawals, incomplete case register forms) we aimed at 100 patients per group, 200 in total. To obtain accurate estimates of the cumulative costs of UVB treatment a consecutive sample of 100 patients (50 per group) was considered to be sufficient, because little variation was expected in treatment duration, number of UVB irradiations, and use of concomitant medication.

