#### Effectiveness

We assessed the effectiveness of both treatments using the Psoriasis Area and Severity Index (PASI) [21] and the Self-Administered PASI (SAPASI) [22]. Both indices evaluate the severity of the psoriatic lesions ànd the area of psoriatic involvement. Their scores vary from 0.0 (no lesions at all) to 72.0 (complete erythroderma of the severest possible degree) [21]. An independent and blinded research nurse administered the PASI during several patient visits to the outpatient clinic. The SAPASI was easier to collect using a questionnaire and was used as an equivalent of the PASI as well as an indicator of the patient's own impression of the extent of the psoriasis lesions [22,23] Both the PASI and the SAPASI were assessed for the whole body, including the lower legs and the scalp. We also determined skin type according to Fitzpatrick's classification of skin phototypes [24,25] and collected data on concomitant use of medication, side effects, demographics and past medical history.

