#### Cost-effectiveness

A direct comparison will be made between the effectiveness of the two therapeutic modalities and their associated cost. Incremental cost per additional patient treated successfully and costs per QALY gained will be estimated. Cost-effectiveness (CE) will be calculated for a time horizon of 12 (11–13) months after randomisation/inclusion. The quality of life (QoL) questionnaires were no longer administered after cessation of irradiation. Based on the association between clinical symptoms and QoL, the impact in terms of QoL for the remaining follow-up, i.e. up to 12 months, will be extrapolated using regression models. Subsequently, cost per QALY can be calculated. In case the difference in effectiveness is less than 15%, we will consider this as equal effectiveness and will limit the economic evaluation to a cost minimisation analysis.

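### The effectiveness analysis compares PASI and SAPASI score differences, but the sample size, the 15% limit and the power claim concern the proportion of responders, so the analysis as written does not address the powered question

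*Protocol article*

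**What the plan says.** **Scale of the design.** The Sample size section defines the outcome: "We considered a 50% or greater improvement in the psoriasis severity from baseline to be a relevant clinical response". It takes from a systematic review that "approximately 85% of the patients treated with UVB show at least a 50% improvement in their psoriasis", and concludes, "with N = 90 per per treatment group and at α = 0.05 and β = 0.20 (power 80"%), that "a reduction in effectiveness from 85% to 70% or less should be distinguishable". The two therapies were expected to perform similarly, and the section calls the calculation a negative trial approach.

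**Scale of the decision.** The Cost-effectiveness paragraph under Outcome assessment makes the limit a rule: "In case the difference in effectiveness is less than 15"%, the therapies count as equally effective and the economic evaluation is reduced to cost minimisation. The Discussion closes by saying that 196 participants give adequate power for a 15% reduction in effectiveness.

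**Scale of the analysis.** Statistical analysis, Effectiveness, says: "Possible differences in effectiveness between the two therapies will be established through comparison of differences in (SA)PASI scores inclusive of 95% CIs". The abstract also describes effectiveness as differences in PASI and SAPASI scores. Neither place mentions a responder proportion or a margin in score points.

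**Instrument.** Outcome assessment, Effectiveness, has a blinded research nurse score the PASI, and says that the patient-completed SAPASI "was used as an equivalent of the PASI" as well as showing the patient's own impression. The Design section states that patients could not be blinded. The analysis paragraph joins the two as (SA)PASI.

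**The concern.** The first research question is whether home treatment is equally effective. A claim of equality needs a limit, and the limit must be on the scale of the estimate. Here the limit is 15 percentage points of responders, while the estimate named for effectiveness is a difference in scores. A confidence interval in PASI points cannot be compared with 15 percentage points.

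Two things depend on the comparison: the answer to the first research question, and the choice between a full cost-effectiveness analysis and cost minimisation. If the scale and instrument are chosen once results are known, that choice can shape both. The instrument matters because the blinded nurse is the trial's main protection against assessment influenced by knowledge of the allocated arm. Treating a score from an unblinded patient as equivalent leaves it open whether the main result keeps that protection.

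**Working it through.** **1. Does the planned size belong to the responder scale?**
Inputs from Sample size: response 85%, limit 15 points, α = 0.05, power 80%, 90 per group. The text does not say whether α is one- or two-sided.

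Non-inferiority, 85% in both arms, one-sided 0.025 (the lower end of a two-sided 95% CI):

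n = 2 × 0.85 × 0.15 × (1.960 + 0.842)² / 0.15² = 0.255 × 7.849 / 0.0225 ≈ 89 per group.

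This reproduces the plan's 90. Power at 90 per group:

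- SE = √(0.255/90) = 0.0532
- 0.15/0.0532 − 1.960 = 0.858, so power is 80.5%.

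Other readings of the same inputs fit less well:

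| Calculation | n per group |
|---|---|
| Superiority 85% vs 70%, two-sided, pooled | 121 |
| Superiority 85% vs 70%, one-sided, pooled | 95 |
| Superiority 85% vs 70%, one-sided, unpooled | 92.7 (93 rounded up) |
| Non-inferiority, one-sided 0.05 | 71 |

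All of these use proportions. The article gives no SD for PASI change and no score margin, so no corresponding calculation can be made for the analysis it describes.

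**2. Could a score difference stand in for the responder difference?**
Only if one determined the other, and it does not. As an illustration, assume that percentage improvement is normal with mean 70% in every case. The SDs are assumptions; the documents give none.

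P(improvement ≥ 50%) = 1 − Φ((50 − 70)/SD)

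| Assumed SD (points) | Responders |
|---|---|
| 20 | 84.1% |
| 30 | 74.8% |
| 40 | 69.1% |

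Arms with SDs of 20 and 40 have the same mean, yet differ by 84.1 − 69.1 = 15.0 points in responders. That is the whole limit. Also, the planned comparison is of score differences, and the same fall in score is a different percentage improvement at different baselines.

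**3. What would the responder comparison deliver?**
98 patients per group were randomised (Table 3: 50 + 48 in each arm). With 85% response in both arms:

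- SE = √(0.255/98) = 0.0510
- 95% CI half-width = 1.96 × 0.0510 = 10.0 points (10.4 with 90 per group)
- 0.15/0.0510 − 1.960 = 0.981, so power against the 15-point limit is 83.7%.

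The trial is therefore large enough for the question, provided that this is the analysis done.

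**The case against.** The strongest reply is that the article already holds what a responder comparison needs. Statistical analysis has a general rule that binary outcomes get a difference in proportions with a 95% CI. Sample size contains the article's only definition of response. Both Cost-effectiveness paragraphs use a cost per additional successfully treated patient, which requires a difference in success proportions. Measurement planning sets 46 treatments as the cutoff for establishing effectiveness, which points to the end-of-therapy reading. An article also condenses a fuller protocol, and outcome hierarchy is often left to that document or to the SAP.

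Much of this stands. A reader might infer that the trial cannot answer its powered question. The documents do not support that: the data and the method are there. A reader might also count instruments, time points and scales and infer a large inflation of error. That does not follow either, because only responder readings have a margin, the readings are correlated, and the 46-treatment cutoff already favours one time point. Nor do the patients who declined randomisation because of a treatment preference show how enrolled patients would score themselves; they were never randomised. Nothing in the text gives SAPASI priority over PASI.

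What the reply does not remove is the conflict between fixed statements. The analysis section does not merely omit a detail. It says how effectiveness differences will be established, and that method is on a different scale from the sample size and the decision rule. The general rule for binary outcomes does not name the 50% response, and success is not defined in either Cost-effectiveness paragraph.

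**Conclusion.** The point holds as a mismatch of scale. As written, the effectiveness analysis does not address the powered question and cannot be read against the 15% limit, although that limit decides equal effectiveness and the form of the economic evaluation. The text also leaves open whether the blinded PASI or the unblinded SAPASI governs.

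The sample size is not in dispute here. It reproduces (89 against 90) if the negative trial approach is taken as non-inferiority at one-sided 0.025. That reading is an inference from the arithmetic, since the article does not state it. The 15-point gap at equal means is an illustration under assumed normal distributions, not a forecast. The 84% power assumes 85% response in both arms and a result for all 98 patients per group; with 90 per group it is 80.5%.

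**What to change.** Replace the sentence in Statistical analysis, Effectiveness, with text such as: *The main effectiveness analysis is the home minus outpatient difference in the proportion of patients with at least 50% improvement in PASI, scored by the blinded research nurse, from baseline to end of therapy or 46 irradiations. Its two-sided 95% CI is read against −15 percentage points. SAPASI, differences in mean scores and the reading at about 23 irradiations are secondary.* Let the equal-effectiveness rule under Cost-effectiveness, and the successful outcome in both Cost-effectiveness paragraphs, refer to this same outcome.

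The cost is one paragraph and a cross-reference, settled before outcomes are compared by arm. The data are already collected, the method is the one the article gives for binary outcomes, and no extra patients are needed. The downside is that the other readings become secondary and cannot carry the claim of equal effectiveness.
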